### Hypotheses and expected results

The PE would be constituted by a larger symptom improvement from Sequence 1 to Sequence 2 in the “medication” Instruction, than in the “control/placebo” Instruction (“medication”(S2-S1)>“control”(S2-S1). This is a general test of the efficacy of the placebo paradigm, which is a crucial building block for assessing the effect of the different Metaphors.

The design does not strictly permit the establishment of equivalence between Metaphors in the sense of a non-inferiority trial, which is deemed too ambitious at this stage. For the proposed protocol, a non-significant difference between VEx and HEx would be considered as a first step to establish the viability of the VEx (HEx = VEx). On a descriptive level, we are expecting a slightly lower effect induced by the VEx, but lower variance than under the HEx, amounting to comparable effect sizes. Beyond that, it is hypothesized that the audio/text Metaphor induces a smaller symptom improvement than the other conditions (HEx = VEx > audio/text) due to absence of visual social cues.

Using a more fine grained analysis at the Trial level could yield additional information, such that groups differ in early or late Trials only, or that the slope (pain changes in consecutive Trials) is different between groups. For example, a significant difference between “medication” vs. “control” could come about by a shallower pain increase in consecutive Trials in Sequence 2, despite identical initial sensitivity (see Fig. 4).

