**Methods:**

To evaluate the virtual experimenter’s efficacy in inducing placebo effects via expectancy manipulation, we suggest a partially blinded, deceptive design with a baseline/retest pain protocol (hand immersions in hot water bath). Between immersions, participants will receive an (actually inert) medication. Instructions pertaining to the medication will be delivered by one of three metaphors: The virtual experimenter, a human experimenter, and an audio/text presentation (predictor “Metaphor”). The second predictor includes falsely informing participants that the medication is an effective pain killer, or correctly informing them that it is, in fact, inert (predictor “Instruction”). Analysis will be performed with hierarchical linear modelling, with a sample size of *N* = 50. Results from two pilot studies are presented that indicate the viability of the pain protocol (*N* = 33), and of the virtual experimenter software and placebo manipulation (*N* = 48).

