**Fig. 1 Fig1:**
[figure not shown]
“[name]”, the virtual experimenter

From this framework, it is easy to manipulate aspects of the instruction or the appearance of the VEx without changing any of the other parameters, as would almost necessarily be the case if the task were performed by a human experimenter (HEx). While virtual reality has been used in some related applications before (e.g., as “virtual reality-based analgesic” distraction techniques [23] or interview partners [24] in the scope of psychological research), its use for the proposed purpose has not been investigated.

In the following, we present a comprehensive study protocol to test the VEx’ efficacy in eliciting PEs, to establish its viability as a substitute for treatment allocation and delivery by a HEx (section “Methods”). Due to the well-documented efficacy of placebo on pain (placebo analgesia), a pain modality will be employed as the method for symptom induction. The protocol combines several features (virtual reality software and pain protocol). These components have been separately investigated in pilot studies presented following the proposed protocol (section “Current status”). We outline the creation of the VEx under “Development of the stimulus material”, and its evaluation under “Pilot study 1”. To assess reproducibility and possible carry-over effects, we conducted a pilot study of the pain protocol, as well. Core findings are presented under “Pilot study 2”.

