## Methods

We propose the following methods to determine the VEx’ efficacy in inducing PEs. The interaction with the VEx will be compared to an HEx interaction, and an audio/text based interaction. All non-interventional interactions such as the pain testing will be performed by a blinded laboratory assistant.

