## Discussion

### Challenges

The two core challenges are the establishment of PEs in a tightly controlled protocol with only limited “dosing” of the placebo manipulation, and achieving a sufficient comparability of the VEx with the HEx interaction as to mimic the psychosocial effects necessary for PEs to arise. The placebo manipulation only contains a verbal expectancy manipulation comparable to those used in other placebo experiments (e.g. [5]). However, we chose to limit emphasis and enthusiasm on the side of the experimenter as much as possible, as to introduce as few as possible confounding factors at this point. This may mean that the PE will not be pronounced.

With the VEx, the greatest challenge is to create a sufficient rapport between him and the participant to be perceived as a social situation. The Ethopoeia concept [45] posits a substrate neutrality of human versus virtual agent behavior: as long as social cues are displayed, they will lead to “mindless responses” [45], p. 83). However, these cues go beyond the behavioral realism of the display (e.g. facial expressions, gestures, blinking, breathing) – which is necessary but not sufficient [46] – and extent to interactional components to attribute agency to the virtual agent, such as turn-taking, visual attention to interlocutors, and behaviors reducing inter-personal distance. While technology like the “rapport agent” exists [47, 48], which has been tailored to naturally engage humans in conversation, our VEx software does not yet exhibit the same capabilities. At this stage, the VEx includes an FAQ module, engaging participants to ask questions with prerecorded answers; furthermore, verbal input will be required from the participants at certain points of the protocol to continue (cf. Fig. 3b). However, in future iterations, actually artificial intelligence-driven conversation is planned [49], engaging participants in personal questions e.g. about demographic variables in a small talk/rapport module.

As to the appearance of the VEx, a balance will be struck between realism and acceptance – specifically, the design has to avoid the so-called “uncanny valley” [50] describing an aversive perception of almost-but-not-quite realistic artificial agents by human spectators.

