### Limitations

The rationale of using the VEx in the context of experimental studies makes the assumptions that the treatment delivery and the accompanying instructions are, in fact, the most important aspects for the generation of PRs. While instructions alone have been shown to effect PEs [5, 51, 52], it has been demonstrated that conditioning paradigms may have better results [6]. However, a conditioning approach was considered too logistically demanding at this stage.

It is possible that the control group itself will not fully believe in the veracity of them only receiving inert medication. However, this would lead to a conservative estimate of placebo effectiveness and is therefore no hazard to the internal validity of the study. We are also considering the option of using a no-treatment control (i.e., no placebo delivery at all) instead of a “control/placebo” instruction.

While evidence exists that female doctors are estimated to have better explanation skills and technical skills and have a higher acceptance [53], the decision to only include male models in the creation of the VEx was made for opportunistic reasons (having a male voice actor available).

On a more general note, while the main intention behind the creation of the VEx is the assessment and abolishment of biases in psychological and medical research, there is a possibility that the use of a virtual agent would induce biases of another sort, such as involving computer (il)literacy or opinions towards technological progress [54]. For example, it is feasible that older participants would have a different response to the VEx’ than younger participants, who will have been exposed to virtual reality technology to a higher extent. On the plus side, there is evidence that participants tend to disclose more personal information to a virtual agent than a human experimenter [55, 56], which may be of relevance with increased interactional capabilities of the VEx. Nevertheless, generalizability will be attempted by using a sample beyond student participants. We are further addressing these issues by post-experiment questionnaires and demographical data about the experience with, and daily use of computers and 3D technology.

Furthermore, the novelty of the simulation may serve to accentuate or alleviate effects which would otherwise be (in)effective. The experience of novelty will be assessed and investigated as a potential moderator of treatment efficacy.

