### Potential and outlook

The broader objective of investigating the VEx is to estimate its comparability to a real human. Using a placebo paradigm is considered an optimal testbed of this comparability due to its dependence on psychosocial variables. Regardless of outcome pertaining to the efficacy of the VEx, results from this study will be disseminated to a wider public, since they will contain valuable information on the specific mechanisms involved in the generation of PEs. Success of the study therefore does not hinge on the efficacy of the VEx, only on replicating results from previous placebo manipulations by the HEx.

Should it be established that the VEx can, in fact, serve as a substitute to an HEx, the possible applications in medical and general psychological research are many. Furthermore, it should be kept in mind that while a VEx would prove to be of great value for placebo research, applicability goes far beyond this narrow topic and extends into most forms of psychological experiments where standardization is of relevance. These applications fall into three interrelated categories – standardization, experimental modification, and communication. To these ends, we are making efforts to develop the software such that it can be easily adopted by other researchers, for whom it would eventually be made available.

Standardization of experimenter characteristics would facilitate the investigation of psychological entities feasibly affected by psychosocial interactions. As no repeated acting/performance would be required, a VEx could serve as a “perfect confederate” [57], p. 6) in social psychological studies, or studies involving social learning. A VEx would get rid of experimenter-side biases due to unblinding, especially if being a stakeholder in an experiment’s success or other factors would incentivize an HEx to guess treatment allocations or behave differently according to which group one is assigned to, introducing experimenter demand characteristics [58].

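### The proceed rule for the virtual experimenter needs only a non-significant VEx–HEx difference, and no stated hypothesis tests the placebo effect within the VEx

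*Protocol article*

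**What the plan says.** **Aim.** The Abstract (Methods) gives the purpose: "To evaluate the virtual experimenter’s efficacy in inducing placebo effects via expectancy manipulation". The end of the Background repeats it: "we present a comprehensive study protocol to test the VEx’ efficacy in eliciting PEs". The opening of Methods speaks of "methods to determine the VEx’ efficacy in inducing PEs".

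**Tests.** The section Hypotheses and expected results defines the PE as a larger improvement from Sequence 1 to Sequence 2 under the medication instruction than under the control instruction. It says of this comparison: "This is a general test of the efficacy of the placebo paradigm", and adds: "which is a crucial building block for assessing the effect of the different Metaphors". The remaining hypotheses compare Metaphors with one another: HEx and VEx alike, both better than audio/text.

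**Decision.** The same section treats a non-significant VEx–HEx difference as a first step towards showing that the VEx is viable. After Fig. 4 it says that the team will go on to more complex protocols if the PEs under VEx and HEx do not differ significantly. It returns to design if the HEx proves superior.

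**Related statements.** Challenges warns of the limited manipulation: "This may mean that the PE will not be pronounced". Potential and outlook says that the study's success does not depend on the VEx, "only on replicating results from previous placebo manipulations by the HEx". Limitations says of control participants who doubt that their pill is inert: "this would lead to a conservative estimate of placebo effectiveness and is therefore no hazard to the internal validity of the study".

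**The concern.** The question asked and the decision taken do not match. Whether the VEx elicits a PE is a question about medication minus inert among participants instructed by the VEx. The proceed rule asks something else, namely whether two PEs can be told apart. Two agents that both work and two that both do nothing give the same answer. So does an imprecise comparison of one that works with one that does not.

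The authors themselves foresee a weak PE. In that case the rule moves the VEx forward on a result that carries no information about it. The general medication-versus-control test does not close the gap. No consequence is attached to its failing, and an effect confined to the HEx can make it significant.

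**Working it through.** **The plan's own figure.** N = 50 with 15% attrition: 50 × 1.15 = 57.5, rounded up to 58 as stated; 50/0.85 = 58.8 would give 59. The gap of one does not affect this point. N = 50 comes from a rule of thumb without alpha, power or effect size, so those are assumptions below.

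**Inputs from Pilot study 2** (n = 33): SD 15.0 in Sequence 1 and 15.5 in Sequence 2; mean shift 46.4 − 40.8 = 5.6; ICC(2,1) = .72.

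**Assumptions:** two-sided alpha 0.05, about equal cells (50/6 = 8.33), 50 − 6 = 44 df (t = 2.015), and the analysis reduced to between-person contrasts on the S2−S1 change. PE sizes are illustrative, since the article gives none.

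**SD of change** = √(15.0² + 15.5² − 2r × 15.0 × 15.5) = √(465.25 − 465r).
- Taking r = .72: √130.45 = 11.4.
- ICC(2,1) also penalises the mean shift. Solving it for r with a shift of 5.6 gives r = .764: √110.1 = 10.5.

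**Precision at N = 50**
- Within-VEx PE: SE = SD × √(2/8.33) = 5.14 to 5.60; 95% half-width 10.4 to 11.3 points.
- VEx–HEx difference in PE: SE = SD × √(4/8.33) = 7.27 to 7.91; half-width 14.7 to 15.9 points, against a Sequence 1 mean of 46.4.

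**Proceed rule as written**
- No PE anywhere: the true VEx–HEx difference is 0, so the chance of non-significance is 1 − 0.05 = 95%. If only an HEx-superior result stops the programme, it is about 97.5%.
- HEx works, VEx does nothing (non-central t, noncentrality = HEx PE/SE): proceed in about 90–91% for an HEx PE of 5 points, 73–76% for 10, and 48–54% for 15.

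**Adding a condition.** Simulation with 100,000 trials per scenario, cells 9/9/8/8/8/8 and SD 10.5 and 11.4. Each extra condition is significance in the expected direction, on top of a non-significant VEx–HEx difference.

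| Extra condition | Proceed, no PE anywhere | Proceed, HEx PE 10, others 0 |
|---|---|---|
| None (as written) | 95% | 73–76% |
| HEx PE | about 2% | 24–27% |
| HEx and VEx combined | about 2% | 18–20% |
| All three Metaphors | about 2% | 13–14% |
| VEx PE | about 2% | about 2% |

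Any PE condition deals with the case where nothing works. Only the VEx contrast deals with the case where the HEx alone works.

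**Power of the VEx contrast:** 14–16% at a PE of 5 points, about 40–48% at 10, and 75–81% at 15.

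**The case against.** The strongest defence is that the article contains the missing pieces. The study is sized to find differences between the six groups, and the main outcome is pain change compared between them, so the model includes the VEx contrast. The general test is called a building block. The proceed sentence speaks of PEs induced by each agent, which presupposes that they exist. Potential and outlook makes replication by the HEx the criterion of success. Equivalence is disclaimed, and proceeding only means more experiments in the same programme.

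Much of this stands, and it limits the point. A reader might infer four stronger things that the article does not support:

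- **That the trial cannot test the VEx.** The 3x2 design can estimate that PE, and an analysis plan not shown here could list the contrast. That the general test averages over Metaphors is itself an inference from its wording.
- **That a null result would be declared proof of the VEx.** Non-significance is called a first step only.
- **That the Limitations sentence on disbelief is wrong.** It concerns the estimate of the PE, and for that dilution is conservative.
- **That audio/text should be dropped from the general test.** At SD 10.5 and PEs of 10 for HEx and VEx, the three-Metaphor test has 59% power against 77% without audio/text if the audio/text PE is exactly 0. If that PE is also 10, the order reverses: 91% against 77%. The article says only that audio/text should be smaller.

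It is also fair that the 95% is simply 1 minus alpha, and that the 73–76% largely reflects a small sample. What does not stand is the claim that the surrounding text supplies the condition. None of those statements is attached to the proceed rule, and an extra contrast in an analysis plan would not change a rule that ignores it.

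**Conclusion.** The point holds for the stated hypotheses and the stated decision rule. The aim concerns the VEx's own PE. No stated hypothesis isolates it, and the rule for moving on can be met without any PE. The 95% figure depends on alpha alone. The 73–76% depends on an assumed HEx PE of 10 points, no VEx PE, N = 50 in about equal cells, and an SD of change of 10.5–11.4 derived from the pilot. The direction holds at the other PE sizes tried. This should be corrected before the study runs, because the rule turns a failed manipulation or an imprecise comparison into a reason to go forward.

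**What to change.** 1. In Hypotheses and expected results, name medication minus inert on the S2−S1 change within the VEx, with its 95% CI, as a key contrast.
2. Report the same contrast within the HEx beside it as the check of assay sensitivity, in line with Potential and outlook.
3. Rewrite the decision paragraph after Fig. 4. Proceeding requires a demonstrated VEx PE, and the VEx–HEx difference is reported as an estimate with its CI. A trial in which no PE is shown is declared uninterpretable for VEx versus HEx.
4. Keep the three-Metaphor instruction test as the general test of the paradigm.
5. Add a note to Limitations that dilution of the PEs, while conservative for estimating them, also favours a non-significant VEx–HEx difference.

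This changes contrast definitions and wording and needs no new data. The price is the VEx contrast's modest power at N = 50 (about 40–48% at a PE of 10 points), so a VEx that does work will often end as not shown. The article should say so.

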### Procedure

Participants will continually rate their pain during Sequence 1 under supervision of a laboratory assistant. They will then be randomly assigned to one of the 3(Metaphor)*x*2(Instruction) experimental groups. In a separate room, they will interact with the Metaphors delivering the Instructions. For the VEx and audio/text condition, interactional components are displayed in Fig. 2b. Crucially, neither assignment will be revealed to the laboratory assistant.

During the placebo manipulation, the inert medication will be automatically dispensed using a self-constructed pill dispenser controlled by an Arduino platform (https://www.arduino.cc/). For VEx and audio/text condition, pill dispension will be performed by the presentation software; in the HEx condition by pressing a button.

An overall inter-Sequence interval of 35 min will be observed for cutaneous sensitivity to recover, and to provide a plausible cover story for the medication to take effect (in the “medication” instruction).

The pain change at retest, compared between experimental groups, will be the main outcome.

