### Analysis and sample size estimation

Data entry is almost fully automated via the touch-screen interface (for continuous pain ratings), a digital survey tool (for other pain ratings and psychological measurements), and on-line registration of physiological parameters. The exception are blood pressure and temperature data which are documented on a score sheet. Continuous pain ratings will be recorded at a sampling rate of ca. 40 Hz, but downsampled to 1 s means for analysis.

Data will be analyzed with hierarchical linear modelling (HLM). Among other strengths, this approach enables us to consider both categorical and continuous predictor variables (e.g., covariates), and the inclusion of cases with missing values, allowing for the number of repeated measures to differ across persons [40]. HLM puts no constraints on the number of repeated measurements, which permits an analysis of differences in the time course of pain. HLM also allows for considering random effects (intercepts and slopes), suitable to the high interindividual variability of pain sensitivity [41].

The robustness of results will be assessed by outlier analyses of the regressional models provided by HLM, including contrasting of predicted versus actual values, studentized residuals and Mahalanobis’ distance. Outliers will be excluded both at the within-person level (individual measurement occasions) and the between-person level (exclusion of individuals with outliers). Robustness will be gauged by changes in the significance of the results.

HLM sample size estimation considers the sample size at level 1 (*n*; in our case, the repeated measurements within-persons) and the sample size at level 2 (*N*; in our case, the individual participants). Recommendations vary (e.g. [42, 43]); Hox [43] suggests larger sample sizes of *n* = 20 and *N* = 50 when investigating cross-level interactions. The wealth of data points provided by the second-by-second continuous pain ratings easily allow for meeting the *n* = 20 suggestion. However, while a total of 600 s of immersions will be available, the effective sample size will be lower due to large intraclass correlations, or strong autocorrelation. Due to the high interindividual variation of pain sensitivity, we would nevertheless aim for including *N* = 50 individual participants to determine difference between the six groups. Estimating 15 % attrition, the projected sample size therefore amounts to *N* = 58 individuals.

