**Fig. 4 Fig4:**
[figure not shown]
Possible results on the Trial level during Sequence 2 (post-intervention): Lower pain increase within the “medication” group (*dashed line*) vs. the “control” group (*solid line*)

If we indeed do not find significant differences of PEs induced by the VEx versus an HEx, we will proceed to more complex protocols (see “Potential and outlook”). If we do find differences such that an HEx proves superior to the VEx, we will return to the design phase and address weaknesses in the VEx software in an iterative design-test protocol until we can reliably elicit PEs using the VEx that are of comparable size with those elicited by an HEx.

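### A non-significant VEx–HEx difference triggers proceeding, but with about 8 people per cell a VEx that induces no placebo effect would often pass

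*Protocol article*

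**What the plan says.** The main outcome is a between-group comparison of change: "The pain change at retest, compared between experimental groups, will be the main outcome". Under Hypotheses and expected results, the PE is the larger Sequence 1 to Sequence 2 improvement under the medication instruction than under the control instruction. The section concedes that the design cannot strictly show equivalence. It then says that "a non-significant difference between VEx and HEx would be considered as a first step to establish the viability of the VEx" and abbreviates this as HEx = VEx.

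After Fig. 4 the same section turns this into a decision: "If we indeed do not find significant differences of PEs induced by the VEx versus an HEx, we will proceed to more complex protocols". If the HEx proves superior, the team returns to design and works "in an iterative design-test protocol until we can reliably elicit PEs using the VEx", with the added requirement that these effects be comparable in size to the HEx's.

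On size, Analysis and sample size estimation cites a source that "suggests larger sample sizes of *n* = 20 and *N* = 50 when investigating cross-level interactions" and concludes that the team would "aim for including *N* = 50 individual participants to determine difference between the six groups". No effect size, SD or power enters.

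**The concern.** A non-significant test shows that two effects are alike only if the test would probably have detected a difference that matters. Here the comparison is a difference of differences between four small cells, so it is imprecise. The less precise the data, the more readily the rule says proceed.

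The Methods section opens with the aim of determining whether the VEx can induce PEs. The proceed rule does not ask that question. A VEx with no effect can pass because the study could not tell it from the HEx. The team would then build more complex protocols on an agent that had not been shown to work.

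**Working it through.** **The plan's own figure.** The text is "attrition, the projected sample size therefore amounts to *N* = 58 individuals", with 15% attrition on 50. 50 × 1.15 = 57.5, which rounds to 58. Dividing instead, 50 / 0.85 = 58.8, or 59. The gap of one person is immaterial. N = 50 is a rule of thumb, so there is no power figure to reproduce.

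**Inputs from the protocol**
- Cells: "They will then be randomly assigned to one of the 3(Metaphor)*x*2(Instruction) experimental groups". No ratio is given, so equal cells are assumed: 50 / 6 = 8.33 each, with 50 − 6 = 44 error df.
- Pilot study 2, continuous ratings, n = 33: means 46.4 and 40.8, SDs 15.0 and 15.5, ICC(2,1) = .72.

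**Assumptions (not in the protocol)**
- Two-sided alpha of 0.05.
- True VEx effect of 0; true HEx effect of 5, 10 or 15 VAS points. The Challenges section warns that the PE may not be pronounced.

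**Step 1: SD of change.** For two occasions, ICC(2,1) = 2c / [s₁² + s₂² + (2/n)(MSC − MSE)], where c is the covariance.
- s₁² + s₂² = 225 + 240.25 = 465.25
- MSC = 33 × 5.6² / 2 = 517.44
- MSE = 232.625 − c
- .72 = 2c / (482.51 + 0.0606c), so c = 177.6 and r = 177.6 / 232.5 = .764
- SD of change = √(465.25 − 355.2) = 10.49

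Reading .72 directly as a correlation gives √(465.25 − 334.8) = 11.42.

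**Step 2: precision.**
- PE in VEx minus PE in HEx (four cells): SE = 10.49 × √(4 / 8.33) = 7.27; 95% CI half-width = 2.015 × 7.27 = 14.65 points.
- Two cells only: SE = 10.49 × √(2 / 8.33) = 5.14. This is also the SE of the PE within VEx.

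**Step 3: chance that an inert VEx passes** (one minus power, noncentral t, 44 df, SD 10.49):

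| True HEx effect | Four-cell PE contrast | Two medication cells only |
|---|---|---|
| 5 points | 90% | 84% |
| 10 points | 73% | 52% |
| 15 points | 48% | 19% |

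**Sensitivity, four-cell contrast**
- With SD 11.42 the column becomes 90%, 77% and 54%.
- With all 58 evaluable (9.67 per cell), the 10-point figure is 69% to 73% across the two SDs.
- The pass rate falls below 50% only above about 1.39 SD of change, roughly 15 to 16 points.
- The smallest PE difference detectable with 80% power is about 20 to 22 points, against a pilot Sequence 1 mean of 46.4.

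**The case against.** The strongest reply is that the protocol is candid. It disclaims equivalence, calls non-significance only a first step, and says under Potential and outlook that success does not hinge on the VEx's efficacy. This stands as to weight: the rule steers the next protocol and does not claim that the VEx can replace a human. It leaves the proceed rule itself unchanged.

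A second reply is that the pooled medication-versus-control test is called a crucial building block, so it may be a precondition. If it were, a simulation puts the chance of an inert VEx passing both tests at about 7% to 31% (HEx effect 0.5 to 1.5 SD of change; audio/text effect zero or half of that). The drop comes mainly from the pooled test's own low power, and that test does not isolate a PE within VEx. The proceed rule does not state this condition. The predicted superiority over audio/text is likewise a hypothesis and not a condition.

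A third is that continuous ratings supply many data points. The protocol itself notes the lower effective sample size, and variation in change between people dominates this contrast.

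Two stronger readings are tempting but unsupported. A reader might infer that non-significance is the expected result whatever the truth. It is not: the pass rate for an inert VEx is 48% at a 15-point HEx effect and 23% at 20 points. A reader might also infer that redesign reapplies the same lenient rule, so that pass rates compound over cycles. The stated end point is a reliably elicited VEx effect of comparable size. Compounding would need an unchanged test, unchanged N and a VEx still inert after redesign, none of which is stated.

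**Conclusion.** The concern holds. As written, a VEx with no placebo effect would pass in about 90%, 73% or 48% of trials at HEx effects of 5, 10 or 15 points on the protocol's own definition of the PE, and in 84%, 52% or 19% if only the medication cells are compared. These rates assume two-sided alpha of 0.05, equal cells, the pilot 2 variability and the stated HEx effects. They would be lower if the pooled test were also required.

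A non-significant result would therefore be weak evidence that the two are comparable, and no evidence in itself that the VEx works. It would be too strong to call this a defect in the study's main conclusion, because the protocol presents the comparison as preliminary and places success elsewhere.

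**What to change.** In Hypotheses and expected results:
1. Delete HEx = VEx as a conclusion from non-significance, and do not treat p > .05 alone as viability.
2. Report the PE within VEx and the VEx-minus-HEx difference in PE, each in VAS points with a 95% CI.
3. Call the comparison inconclusive when the CI for the difference still includes loss of the whole HEx effect.
4. Make proceeding depend also on evidence of a PE within VEx. Tested at the 2.5% upper tail, an inert VEx would meet that condition about 2.5% of the time.
5. Report every redesign cycle, including those that failed.

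These are wording changes that need no new measurements, but they have a cost. With a half-width of 14.65 and the HEx effect taken at its estimate, item 3 gives inconclusive unless the observed VEx effect exceeds about 15 points. The within-VEx test has only about 48% power at a true 10 points. At this size inconclusive is the likely verdict. For 80% power to detect loss of the whole HEx effect, the four-cell contrast would need about 126, 50 or 32 people per cell at HEx effects of 0.5, 0.8 or 1.0 SD of change.

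A formal margin is an option, but it brings back the non-inferiority test that the protocol declined. With SE 7.27, a VEx truly equal to the HEx would clear a margin of 5, 10 or 15 points only about 10%, 27% or 52% of the time.
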